## Abstract

**Background and Rationale:** Among the key players in the pathogenesis of Amyotrophic Lateral Sclerosis (ALS), microglia and T regulatory lymphocytes (Treg) are candidate cells for modifying the course of the disease. The gut microbiota (GM) acts by shaping immune tolerance and regulating the Treg number and suppressive function, besides circulating neuropeptides, and other immune cells that play in concert through the gut-brain axis. Previous mouse models have shown an altered enteric flora in early stage ALS, pointing to a possible GM role in ALS pathogenesis. Fecal Microbial Transplantation (FMT) is a well-known therapeutic intervention used to re-establish the proper microenvironment and to modulate enteric and systemic immunity.

**Methods:** We are going to perform a multicenter randomized double-blind clinical trial employing FMT as a therapeutic intervention for ALS patients (NCT0376632). Forty-two ALS patients, at an early stage, will be enrolled with a 2:1 allocation ratio (28 FMT-treated patients vs. 14 controls). Study duration will be 12 months per patient. Three endoscopic procedures for intestinal biopsies in FMT and control groups are predicted at baseline, month 6 and month 12; at baseline and at month 6 fresh feces from healthy donors will be infused at patients in the intervention arm. The primary outcome is a significant change in Treg number between FMT-treated patients and control arm from baseline to month 6. Secondary outcomes include specific biological aims, involving in-depth analysis of immune cells and inflammatory status changes, central and peripheral biomarkers of ALS, besides comprehensive analysis of the gut, saliva and fecal microbiota. Other secondary aims include validated clinical outcomes of ALS (survival, forced vital capacity, and modifications in ALSFRS-R), besides safety and quality of life.

**Expected Results:** We await FMT to increase Treg number and suppressive functionality, switching the immune system surrounding motorneurons to an anti-inflammatory, neuroprotective status. Extensive analysis on immune cell populations, cytokines levels, and microbiota (gut, fecal and saliva) will shed light on early processes possibly leading the degenerative ALS course.

**Conclusions:** This is the first trial with FMT as a potential intervention to modify immunological response to ALS and disease progression at an early stage.

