### Outcome Measures

Primary outcome measure is the modification from baseline to month 6 in Treg number in transplanted ALS patients compared to the control arm (26).

Secondary outcome measures include the following:

✓ Biological outcome measures:–Change from baseline to month 3, 6, 9, 12 of the T cell distribution especially the ratio Treg/Th1 or Treg/Th17 comparing FMT arm and control arm (both blood—at each time point, and small intestine—only at 6 and 12).–Changes from baseline to month 3, 6, 9, 12 in inflammatory status (cytokine profile) comparing FMT and control arm (in blood and feces at each time point, and in CSF at month 6).–Changes from baseline to month 3, 6, 9, 12 between FMT arm and control arm in the following biomarkers: creatinine, albumin, CK, vitamin D, plasma/CSF neurofilament heavy/light chain protein.–Biological modifications from baseline to month 6 and 12 in the composition of saliva, gut and fecal microbiota (including SCFA) comparing FMT and control arm.✓ Safety: will be assessed in FMT and control arm considering the occurrence of AEs and modifications in physical examination, vital signs, body weight, and laboratory tests (biochemistry, hematology) during and following the treatment.✓ Clinical outcome measures:The following clinical variables will be compared between FMT and control arm:– Change from baseline to each time point (month 1, 3, 6, 9, 12) of ALSFRS-R.– Survival from onset and randomization to death or tracheotomy.– Change of Forced Vital Capacity (FVC) from baseline to each time point (month 1, 3, 6, 9, 12).– Frequency of procedures (PEG, NIV, IV) from baseline to month 3, 6, 9, 12.✓ Quality of life: will be assessed as the change in absolute and relative values of the Amyotrophic Lateral Sclerosis Specific Assessment Questionnaire (ALSAQ40) from baseline to month 6 and 12 in FMT and control arm.

The Table 3 shows the study flow chart.

**Table 3 T3:** Study flow chart.

	**Pre-treatment**		**Treatment**					**Follow up**			**Study end**
**Examinations**	**Screening**	**Baseline (W0)**	**FMT 1 (Rome)**	**M1**	**M3**	**M6**	**FMT 2 (Rome)**	**M7**	**M9**	**M12 (Rome)**	**M12**
**Time window**		** <3 weeks from screening**	** <4 weeks from screening**	**±3 days**	**±3 days**	**±3 days**	**±7 days**	**±7 days**	**±7 days**	**±7 days**	**≥7 days <4 weeks from M12**
Informed consent	x										
Medical history	x										
Inclusion exclusion criteria	x										

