### Role of Participating Centers

This multicenter study will involve nine Italian Units: six referral ALS Centers (located in Florence, Chieti, Perugia, Modena, and Rome), three renowned laboratories, one endoscopy service and a statistical unit.

ALS is a rare disease with fast progression and no effective treatment, which requires a solid methodological, clinical approach, and biological background for clinical trials conduction.

Each clinical center is expected: (I) to randomize at least seven patients according to including and excluding criteria in 18 months; (II) to provide one principal investigator to evaluate including and excluding criteria, and assess primary and secondary outcomes; (III) to adhere to ALS management guidelines of the European Federation of Neurological Societies(in particular as regards ventilation and nutrition issues).

The analysis of biomarkers will be centralized and performed in two internationally renowned laboratories Laboratory of Microbiology Policlinico Gemelli in Rome and Laboratory of Immunology, Department of Experimental and Clinical Medicine—University of Florence, and FMT will be performed at Policlinico Gemelli in Rome, a leading European Center for this kind of treatment.

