### Data Analysis

Data will be collected by investigators through electronic CRF, which will be conveyed to the trial database. At trial completion, data from the locked database will be extracted for analysis by an expert statistician.

Separate analyses will be performed in:

All randomized subjects receiving at least 1 FMT (Intention-to-treat population).All randomized subjects excluding protocol deviations (Per protocol population).

As far as biological activity is concerned, immune response to FMT will be analyzed as a difference in positive response to FMT between the control group and the FMT group, assessed by comparison of proportion of patients in the two groups showing a mean Tregs increase by at least 20%, between baseline and month 6 measurements.

Mean values of different T, B, NK cell subpopulations, neurodegeneration biomarkers, and cytokines will be assessed and mean differences in plasma concentrations between the two treatment arms will be calculated using *t*-test or Wilcoxon-Mann-Whitney test as previously reported (26). ANOVA will be used for assessing the mean change over time for the same variables as above, with treatment as between-subjects factor and time as within-subjects factor. Different models will be used, each with a different biomarker of activity as the dependent variable. Models will be adjusted for any unbalanced distribution of the main prognostic factors (e.g., age) between the two treatment arms, according to previously published statistical methods (26).

Analysis of microbiota will be performed with specific software.

Record of any AE and SAE will be kept for every subject receiving at least one round of FMT till the study completion, performing safety analysis accordingly.

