As for clinical outcome measures, we will compare ALSFRS-R total score and subscores (bulbar, respiratory, gross, and fine motor) changes from baseline to each time point in treatment arm vs. control arm. Frequency of procedures (PEG, NIV, IV) will be compared from baseline to each time point in treatment vs. control arm. The comparison of clinical endpoint among arms will be carried out by using the logistic regression model. Results will be presented as odds ratios (OR) and 95%C.I. FMT will be considered effective in relation to controls whether the OR of positive results will provide a *p* < 0.05. Change in FVC during the study will be analyzed using a mixed model for repeated measures (MMRM). Difference between treatment groups and two-sided 95% CI will be estimated .Log-rank tests via Kaplan-Meier method will be employed to compare differences in tracheostomy-free survival between the two treatment arms (from onset and from randomization), while Cox's proportional hazard model will be used for adjusting for any possible unbalanced prognostic factors. Statistical significance will be set at 0.05 level for a two-tailed test. Last observation will be considered for patients with missing data.

Given the short duration of the study, an interim analysis of efficacy data is not scheduled. Nevertheless, to address safety concerns, a report including all relevant clinical data of patients will be sent by the Statistics Unit to an independent Data and Safety Monitoring Board for scheduled DSMB meetings (also through Skype) when 14 patients would have completed the second treatment and then every 6 months.

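### Last observation carried forward is the only missing-data rule; it is unsuited to declining ALSFRS-R and FVC scores and sits badly with the MMRM planned for FVC

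*Protocol article*

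**What the plan says.** The Data Analysis section of the protocol article ends its paragraph on clinical outcomes with "Last observation will be considered for patients with missing data". The sentence names no endpoint, no reason for missingness and no exception. No other missing-data method and no sensitivity analysis is given.

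The same paragraph covers three kinds of clinical analysis:

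- **ALSFRS-R:** "we will compare ALSFRS-R total score and subscores" as changes from baseline, by arm. Outcome Measures lists the visits: "Change from baseline to each time point (month 1, 3, 6, 9, 12) of ALSFRS-R".
- **FVC:** "Change in FVC during the study will be analyzed using a mixed model for repeated measures (MMRM").
- **Tracheostomy-free survival:** log-rank and Cox analyses. Outcome Measures defines the endpoint as "Survival from onset and randomization to death or tracheotomy".

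The Treg responder comparison and the biomarker analyses come earlier in the section. For the biomarkers, "ANOVA will be used for assessing the mean change over time for the same variables as above". That text mentions no imputation.

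On the disease itself, Role of Participating Centers says "ALS is a rare disease with fast progression and no effective treatment". The Abstract gives the follow-up: "Study duration will be 12 months per patient".

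**The concern.** Carrying the last observation forward assumes that nothing changes after a patient's last visit. The protocol's own description of ALS says the opposite. A patient last seen at month 3 would enter the month-12 comparison with the month-3 score, which is better than the true score would have been. The arm that loses more patients, or loses them earlier, then looks more stable than it is. The size of the error grows towards month 12.

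The rule also clashes with the FVC analysis in its own paragraph. An MMRM uses the visits that were observed, under a missing-at-random assumption, and needs no filled-in values. If FVC is filled first, the model receives flat invented profiles as if they were data.

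What is at stake is mainly the secondary clinical endpoints. The Introduction and Anticipated Results say the trial is meant to prepare a later efficacy study, so a distorted estimate of functional decline would be passed on to that study's design.

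**Working it through.** No figure in the plan depends on this rule. The planned 42 patients stay the same with or without it. The check is therefore an illustration of the bias in the month-12 change in ALSFRS-R.

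**Inputs from the document**

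- Visits at months 1, 3, 6, 9 and 12 (Outcome Measures).
- Average drop-out of 10% (Sample Size Estimation).

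**Assumptions not in the document**

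- Linear decline of s = 0.5, 1.0 or 1.5 ALSFRS-R points per month, the same in both arms, so there is no true effect.
- Drop-outs decline at the same rate as completers.
- A drop-out's last visit is equally likely to be month 1, 3, 6 or 9.

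**Formulas**

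- Points wrongly credited to one patient at month 12 = s × (12 − last month seen).
- Shift in an arm mean = drop-out share × s × mean of (12 − last month seen).
- Bias in the contrast = shift in the FMT arm − shift in the control arm.

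**Step 1: one patient.** At s = 1, a patient last seen at month 3 is credited with 12 − 3 = 9 points, and one last seen at month 6 with 12 − 6 = 6 points.

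**Step 2: average over last visits.** Mean last visit = (1 + 3 + 6 + 9) / 4 = 4.75 months. Each drop-out is spared 12 − 4.75 = 7.25 months of decline on average.

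**Step 3: the plan's 10% in both arms.** Each arm mean looks better by 0.10 × s × 7.25 = 0.36, 0.73 or 1.09 points for s = 0.5, 1.0 or 1.5. The shifts are equal, so the bias in the contrast is 0.

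**Step 4: unequal amount, 20% in FMT and 10% in control.** Bias = (0.20 − 0.10) × s × 7.25 = 0.36, 0.73 or 1.09 points in favour of FMT. With the percentages swapped, the sign reverses.

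**Step 5: equal amount, unequal timing.** Take 10% in both arms, with last visits at month 3 in one arm and month 9 in the other. Bias = 0.10 × s × (9 − 3) = 0.3, 0.6 or 0.9 points in favour of the arm that loses patients earlier.

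**Step 6: reach of the rule, by setting the texts side by side**

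- ALSFRS-R and FVC are in the same paragraph as the rule, and neither is exempted.
- The survival analyses are in that paragraph too, but a patient who leaves is censored there, so no value is carried forward.
- The Treg and biomarker analyses stand earlier in the section. The unqualified wording could cover them, but the text does not say so.
- Death is a component of the survival endpoint. Nothing says what happens to functional scores after it.
- If the rule does reach Treg, Table 3 matters. The Treg sample around month 6 is marked under the second FMT visit in Rome, not under the M6 visit. A patient who misses that visit would receive the month-3 value or, failing that, the baseline value, which means no increase and hence no response.

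**The case against.** The strongest defence is that the sentence is short, closes a paragraph on clinical outcomes, and can be read as covering only the visit-by-visit comparisons, with the MMRM left to handle FVC on observed data. The affected endpoints are secondary in an exploratory trial. At the plan's own 10% drop-out, if equal and similarly timed, the contrast is not biased at all (step 3). All of this stands as a limit on scope and size. It does not rescue the method for ALSFRS-R, where carry-forward applies on any reading. Nor can the point be left to an analysis plan, because the protocol names the method outright.

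A reader might infer more than the document supports:

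- **That the rule governs every endpoint, including Treg and the repeated-measures ANOVA.** The wording permits this but does not state it.
- **That patients who die are credited with preserved function.** The document is silent on scores after death; it does not say they are carried forward.
- **That the rule strictly contradicts the MMRM.** An MMRM can be run on filled data. The clash is between assumptions.
- **That standard errors will be too small.** This is not generally true. Mixing scores frozen early with fully progressed ones can raise the variance between patients.
- **That the bias is 0.9 or 1.8 points.** At 1 point per month, 0.10 × 9 = 0.9 is a shift in one arm's mean, which cancels under equal drop-out. The figure 0.20 × 9 = 1.8 needs 20% loss in one arm, none in the other, and every loss at month 3. Nothing in the document points to that pattern.

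**Conclusion.** The concern holds in a limited form. As the only stated rule, carry-forward is a badly chosen method for ALSFRS-R and FVC. It overstates retained function for patients who leave early, and it biases the comparison between arms whenever drop-out differs in amount or timing. The direction cannot be known in advance. It is also at odds with the assumptions of the MMRM planned for FVC, and the text does not say which prevails.

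For 20% versus 10% drop-out, the false month-12 difference in ALSFRS-R is about 0.36 to 1.09 points, or 0.73 at 1 point per month. This rests on an assumed linear decline and evenly spread last visits. If faster decliners leave first, each carried-forward score is further from the truth.

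Whether the rule reaches scores after death, Treg or the biomarkers is unclear and must be stated. The log-rank and Cox analyses are not affected. The change should be made, but the harm shown is mainly to secondary endpoints.

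**What to change.** 1. Delete the carry-forward sentence.
2. Analyse FVC and change in ALSFRS-R with an MMRM on observed data, with terms for arm, visit, arm by visit, baseline and the ΔFS stratum used at randomization. Use the same model for the repeated continuous biomarkers in place of the repeated-measures ANOVA.
3. State that functional scores are not carried forward past death, and add a joint rank of survival and function as a sensitivity analysis.
4. An MMRM does not serve the binary Treg responder endpoint. State one primary rule for it, applied equally in both arms, for example that a missing month-6 value counts as non-response. Add an observed-case sensitivity analysis, and do not substitute the month-3 value.
5. Deleting the sentence also leaves the comparison of PEG, NIV and IV frequency without a rule, so add one line on how patients who leave early are counted there.

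The cost is analysis wording and a little more analysis work. No visit, sample or patient is added, and the sample size does not change.

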### Ethics Approval

This study has been approved by Comitato Etico Area Vasta Emilia Nord on July 2018 (prot. n. 0010722/18), and by National Transplantation Center on 29 March 2019.

The trials has been registered in clinicaltrials.gov (NCT03766321).

## Discussion

### Choice of Treatment

FMT dates back to fourth-century China, as a report of a traditional Chinese medicine doctor describing a patient's recovery from food poisoning and severe diarrhea after treatment with oral human fecal suspension (32). Further uses of this kind of treatment have been described since the sixteenth century (32–35) mainly through retention enema.

More recently, FMT has emerged as a safe and effective treatment for the management of recurrent, and possibly refractory, *Clostridium Difficile* Infection (CDI) by restoring gut microbial diversity, with cure rates >85% (36). Currently, the FMT has been approved for the treatment of this condition, for which it has had unanimously excellent results (24, 37, 38).

Since a perturbed microbiota is associated with several diseases, it is conceivable that microbiota restoration therapies could be useful in their management (24). The importance of “healthy” gut microbiome has been shown in oncology, an in detail in relation to response to antitumor treatment (39–41). In addition, a few papers have recently highlighted a potential link of gut dysbiosis and neurological diseases (41–45), such as multiple sclerosis (46, 47), Parkinson's Disease (48, 49), and Alzheimer's disease (50, 51).

For this reason, there are studies now testing FMT potentiality to treat multiple sclerosis, myasthenia gravis, Parkinson's Disease, and epilepsy (22, 52).

Some preliminary data place the theoretical basis for a GM involvement in ALS because immune system, which plays a key role at least in ALS progression, can be modulated through gut-brain axis. Indeed, the gut environment favors the generation of autoreactive T-cells with unique regulatory functions, important for preventing CNS autoimmunity (53). Some commensal bacteria can induce Tregs development and FMT determine Tregs' increase (54).

Moreover, alterations in GM composition in ALS have been reported in previous studies. Fang et al. (55) found a significantly increased population of harmful microorganisms (genus *Dorea*) with reduced population of beneficial microorganisms (genus *Oscillibacter, Anaerostipes, Lachnospiraceae*) in ALS patients (45). The authors suggested that the imbalance in intestinal microflora constitution may cause a pro-inflammatory dysbiosis that may alter the intestinal epithelial barrier, promoting immune/inflammatory responses with a major role in ALS pathogenesis.

Another study (56) detected a higher amount of *E. Coli* and *Enterobacteria* and a low presence of total yeast in the GM composition of ALS patients with respect to healthy controls.

Two pre-clinical researches, performed in G93A animals, studied the correlation between gut dysbiosis, altered intestinal permeability and enteric inflammatory/neurogenic responses (12). Wu et al. (57) found signs of leaky intestine in a G93A transgenic mouse having an augmented gut permeability due to impairment of the intestinal tight junction structure and related protein expression, if compared to wild-type mice (57). The same model showed a reduced number of and an altered function of epithelial Paneth cells, that impact the GM and have a role in the innate immune response, and, as far as concerns GM composition, a lower abundance of butyrate-producing bacteria such as *Butyrivibrio fibrisolvens, Escherichia coli*, and *Firmicutes* was detected. Finally, shifts in the gut microbiome included.

Likewise, Zhang et al. (58) reported a correlation between gut dysbiosis and morphofunctional alterations of intestinal permeability in the same model, since the earliest stages of the disease. They demonstrated the presence of SOD1 aggregates, which are distinctive of ALS associated to SOD1 mutations in animal models and in patients, not only in neurons and skeletal muscle, but also in the intestine of ALS mice and human intestinal epithelial cells. Moreover, the authors observed that, following treatment with 2% butyrate (a natural bacterial product able to restore the intestinal microbial homeostasis), G93A mice restored GM balance and intestinal epithelial barrier integrity, besides they showed improved central and peripheral symptoms of the disease, prolonged survival, and slowing of weight loss (58).

These data suggested that changes in GM, impaired intestinal permeability and enteric inflammation represent one of the earliest events in ALS. However, these findings did not allow to firmly establish whether the alterations of the enteric bacteria neuro-immune network contribute to the ALS pathophysiology, or whether they happen as a consequence of the cascade of events accompanying neurodegeneration (12).

In a recent study, SOD1-Tg mice prone to ALS showed a vivarium-dependent pre-symptomatic dysbiosis and an altered configuration of metabolites, occurring with a disease worsened under conditions of germ-free or broad-spectrum antibiotic treatment (59). The authors could correlate some species in gut microbiota with ALS severity and supplementation with certain species changed mice phenotype (59).

In this context, FMT may act against ALS progression, by regulation of the mutual signaling between gut microflora and CNS (11), employing bidirectional communication (via neuronal, hormonal, immunologic, and toxic signaling) (14, 15). Moreover, direct communication through the vagus nerve, changes in tryptophan and norepinephrine metabolism, production and absorption of neuroactive metabolites, immune activation through molecular mimicry and the direct production of neurotoxins (22) may be useful in controlling ALS disease) (13). Nearly 30% of ALS patients show autonomic dysfunctions with demonstrated involvement of the intermediolateral columns and the Onuf nucleus. The vagal nerve could be a route for GM and brain communication (60). Of note, GM has been found to interact with ENS-vagus nerve pathways (61) because, bacterial derived-neurotransmitters and neuropeptides can activate directly myenteric neurons, which, through vagal nerve ascending fibers, deliver nerve inputs to the brain (12, 62).

Enteric bacteria and their metabolites (especially the SCFAs) can indeed induce enterochromaffin cells to release neurotransmitters and neuropeptides (including peptide YY, neuropeptide Y, cholecystokinin, glucagon-like peptide-1 and−2, and substance P), which, in turn, can reach the brain through blood circulation and have an effect on CNS functions (12). In addition, the intestinal epithelium regulates the spread of specific bacterial products (e.g., SCFAs, vitamins or neurotransmitters, such as acetylcholine, dopamine, noradrenaline, gamma-aminobutyric acid, or serotonin) into the circulatory system, that, in turn, may arrive to the CNS (11, 12). In this way, circulating microbiota-derived metabolites, neuropeptides, and neurotransmitters can enter the CNS and so directly influence the neurobiology and the ALS pathology.

Individual case reports of ALS patients documented benefits as a result of FMT (63). This research field is therefore highly innovative and is gathering increasing interest from the international scientific community (13, 43).

